## Abstract

**Background:**

The ageing population requires seamless, integrated health and social care services in the community to promote the health of older adults. However, inadequate financial resources, a lack of clear operational guidelines, and various organisational work cultures may affect the implementation quality and sustainability of these services. As a unique approach, this study seeks to examine the preliminary effects of a health-social partnership programme on the health self-management of community-dwelling older adults in Hong Kong. Additionally, the study seeks to ascertain key insights into the mechanisms and processes required to implement and sustain a self-care management programme in broader practice in community settings.

**Methods:**

This study will use a hybrid effectiveness-implementation design. During the 3-month programme, subjects in the intervention group will receive four Zoom video conference sessions and four telephone calls conducted by a health-social service team that will include a nurse case manager, community workers, general practitioners, a Chinese medicine practitioner, and social workers. Subjects in the control group will receive a monthly social telephone call from a trained research assistant to rule out the possible social effect of the intervention. The reach, effectiveness, adoption, implementation, and maintenance framework (i.e. RE-AIM framework) will be used to evaluate the implementation and effectiveness outcomes. Of the five dimensions included in the RE-AIM framework, only effectiveness and maintenance outcomes will be collected from both the intervention and control groups. The outcomes of the other three dimensions—reach, adoption, and implementation—will only be collected from subjects in the intervention group. Data will be collected pre-intervention, immediately post-intervention, and 3 months after the intervention is completed to evaluate the maintenance effect of the programme.

**Discussion:**

This programme will aim to enhance health-promoting self-care management behaviours in older adults dwelling in the community. This will be the first study in Hong Kong to use the hybrid effectiveness-implementation design and involve key stakeholders in the evaluation and implementation of a health self-management programme using a health-social service partnership approach. The programme, which will be rooted in the community, may be used as a model, if proven successful, for similar types of services.

**Trial registration:**

Clinicaltrials.gov, NCT04442867. Submitted 19 June 2020

**Supplementary Information:**

The online version contains supplementary material available at 10.1186/s40814-023-01412-0.

## Background

The rapid increase in life expectancy is outpacing the increase in healthy life expectancy, implying that people are living their extended years with multiple morbidities and complications, physical and cognitive impairment, and frailty [1]. Such complex conditions often lead to challenges with self-care (that is the ability to establish behaviours to promote and maintain one’s health and well-being) for older adults along the health and illness trajectory. In conjunction with knowledge deficits and inadequate social support, self-care activities become increasingly laborious for these individuals [2]. Despite these challenges, self-care activities, including health maintenance, illness prevention, and monitoring and managing healthcare activities, are performed by the older adults and their primary caregivers with limited assistance from healthcare professionals [3]. Increasing awareness and efforts have been devoted to supporting and empowering older adults to perform self-care activities. Evidence shows that this support is pivotal to maintaining, restoring, and improving health and well-being; reducing morbidity, mortality, and healthcare service utilisation rates and the associated costs; and enabling elderly individuals to live independently in the community [4].

As a result of the complicated conditions experienced by older adults, the level of demand for care changes continuously, from an emphasis on providing care in silos to offering interprofessional care [5]. Although there is a comprehensive range of health and social services provided in developed countries [6], the integration of health and social care is still nascent [7]. Many older adults regard health and social services as arduous to comprehend, necessitating the assistance of healthcare professionals to ensure service continuity [5, 6]. A coordinated health and social service partnership may deliver more consistent, continuous, appropriate, and timely services to older adults, and thus achieve favourable health outcomes [8–12]. By minimising redundancies and inconsistencies, services may become more accessible and efficient for older adults with chronic diseases, who require care from different disciplines [8–12].

To address the complex needs of older adults and the fragmentation of health and social care provision, our research team previously implemented a nurse-led, health-social service partnership programme (HSPP) that included proactive comprehensive care assessment, goal setting, self-care self-efficacy enhancement, and coordinated health and social services for a group of community-dwelling older adults [9]. The programme was found to be effective at improving self-efficacy, medication adherence, and quality of life and reducing the utilisation of health services [13]. Other randomised controlled trials using health and social care approaches to address the self-care challenges of older adults with low income and frailty have also reported positive effects on general health and the ability to perform activities of daily living (ADLs) and instrumental ADLs, and reduced hospitalisation rates [14, 15].

Although an increasing number of studies show that a coordinated health-social service partnership approach is useful to facilitate self-care amongst older adults, these studies have used a randomised controlled research design and have been tightly controlled for confounding variables [16]. When implementing a programme in a real-world setting, factors such as heterogeneous samples and settings, attitudes, relationship and organisational cultures of the service providers, and resources and costs may affect the successful adoption and sustainability of the programme [17]. The adaptive process of an intervention in a real-world setting is dynamic and often generates unpredictable issues that require an immediate response from those implementing the programme [17]. A clear conceptualisation and description of the intervention should be delivered to those delivering the programme to ensure that they are capable of adapting the intervention to their own care settings [18]. The degree of constraint at the time of implementation should be determined to allow the effective core components to be maintained under tolerable alterations, and thus, allow the successful adaptation of the intervention with sustained fidelity [19]. Implementation science focuses on the adoption of interventions by systems of care under real-world conditions [20]. All aspects of implementation, including factors affecting implementation, such as the implementation processes and outcomes, generalisation, and continuity, are investigated, with context and users as important components [21]. In a conventional effectiveness study, the barriers to implementation fidelity are often unclear, resulting in frustration and failure to maintain the effectiveness of the programme at the level demonstrated in efficacy trials [22].

To overcome the potential difficulties in translating effective intervention programmes from research to practice, our team aims to conduct a pilot study using a type 1 hybrid effectiveness-implementation design. We used the definition of pilot study that proposed by Eldridge and colleagues [23]. They suggested that pilot study is a subset of feasibility studies that specifically examines a design feature proposed for the main trial, but on a smaller scale. With balanced foci on effectiveness and implementation, the type 1 hybrid design provides an authentic examination of the effectiveness of a programme, while accelerating the translation process [22]. This design also incorporates the shared vision of different stakeholders early in the process of programme development to dynamically address the barriers to and facilitators of implementation, while complementing the direction of the research with system, provider, and client needs [24]. Similar hybrid studies and other implementation studies have addressed the self-care challenges of community-dwelling older adults, but these studies have only focused on either the health or social service domains individually [25, 26]. By gathering information about both effectiveness and implementation strategies, this study aims to provide key insights into the mechanisms and processes required to implement and sustain a self-care management programme in broader practice in community settings.

### Objectives

To evaluate the process of implementing a nurse-led HSPP programme in a community centre, which will include the aspects of the following: *Reaching* into the target population, potential *Effectiveness* of the programme when compared to a monthly social telephone call, *Adoption* by the staff and participants, *Implementation* fidelity, and *Maintenance* over time. Specifically, these aspects are defined as follows:i)Reach: recruitment rate of the programme.ii)Potential effectiveness: self-efficacy, quality of life (QoL), health service utilisation (i.e. the total number of unscheduled general out-patient department, general practitioner, and emergency room visits and hospital admissions and the total number of attendances at health services).iii)Adoption: perceptions on the facilitating factors of and barriers to program adoption in the community centre.iv)Implementation: fidelity of the programme.v)Maintenance: sustained programme effects at 6 months.

### Conceptual framework

The hybrid effectiveness-implementation design of this study will be guided by several theories and frameworks. The design of the HSPP intervention will be informed by Bronfenbrenner’s ecological systems theory [27], which asserts that self-care is influenced by factors at the following three levels of the environment: the microsystem, mesosystem, and macrosystem [27]. The microsystem level consists of modifiable personal factors, such as self-efficacy. The mesosystem level focuses on the interrelationships between older adults and the persons who have close connections with them, such as their healthcare providers. The macrosystem level is an extension of the mesosystem level and involves cross-boundary relationships between the different organisations. Based on this theory, the self-efficacy of an individual at the microsystem level may be enhanced when a health-social care service partnership structure is formed at the macrosystem level, with support from healthcare providers at the mesosystem level. Improvements in self-efficacy may promote the self-care management of an individual in the community [28].

The implementation process of the study will be guided by the implementation framework described by Durlak and DuPre [29]. This framework emphasises the following five key components that are required in implementation research: (1) innovation characteristics, such as adaptability and compatibility; (2) provider characteristics, such as self-efficacy and skill proficiency; (3) community factors, such as funding allocation and policy directives; (4) factors associated with the intervention delivery system, such as staffing considerations and organisational factors; and (5) factors associated with the intervention support system, such as staff training sessions and technical assistance. The study will incorporate these components in the implementation process.

The reach, effectiveness, adoption, implementation, and maintenance (RE-AIM) framework will be used to guide the evaluation of the effectiveness and implementation outcomes [30]. The RE-AIM framework was considered for inclusion as it is helpful in ascertaining not only the impact of an intervention/ programme, but also the context wherein it is implemented and associated contextual factors [30]. Thus, this framework is congruent with the notion of implementation science and commensurate to the aims of the current study. This framework measures the following five dimensions: (1) the reach into the target population, (2) the potential effectiveness of the intervention, (3) adoption by staff and the setting, (4) implementation fidelity, and (5) implementation maintenance (i.e. the degree to which the programme is sustained over time).

## Methods/design

This protocol paper has been reported in accordance with extension guidelines to the Consolidated Standards for Reporting and Writing a pilot or feasibility trial [23, 31] and the standards for reporting implementation studies statement [32]. The SPIRIT statement was found in Supplementary file. The programme was approved by the Human Subjects Ethics Application Committee of the Hong Kong Polytechnic University (No. HSEARS20201130001).

### Study design

A type 1 hybrid effectiveness-implementation design will be used in this pilot study. This design takes a dual focus in testing effects of a clinical intervention on relevant outcomes while observing and gathering information on implementation [21].

### Study setting, subjects, and recruitment strategies

The study will be implemented in a community centre operated by a non-governmental organisation. The centre provides social activities to the community-dwelling older adults and support services to their informal caregivers. Members of the community centre will be screened and recruited to the study if they (1) are aged at least 60 years, (2) currently use a smartphone, and (3) score 22 or more in the Hong Kong version of the Montreal Cognitive Assessment (HK-MoCA) [33]. Elderly individuals will be excluded if they (1) unable to communicate, (2) are not living at home, (3) are bedbound, (4) are living in an area with no Internet coverage, (5) have already participated in another structured community health and social service partnership programme, or (6) will not be staying in Hong Kong for the next 3 months.

A staff in the centre who will not involve in recruitment and the project will provide a member list to the research team. A trained research assistant (RA) will screen the member list and make sure the potential subjects will fit for the inclusion and exclusion criteria before making phone calls to them. After briefly introduce the programme to potential subjects through phone call, the RA will arrange a home visit with them to fully explain the procedure of the programme and obtain their consent forms. The RA will collect the baseline data of those who agree to participate. After successfully collecting their data, the RA will call the principal investigator (PI) of the research team for group randomisation. The subjects will be randomly assigned in a 1:1 ratio to either the intervention group or control group. Random group assignments will be generated by the PI using Research Randomizer software (i.e. 1 = intervention group; 2 = control group). These group assignments will then sealed in envelopes and opened sequentially by the PI after receiving the call from the RA. The RA and the community centre staff, but not the PI or the healthcare providers, will be blinded to the group assignments. The PI will neither involve in recruitment process nor data collection. To prevent contamination between the intervention and control groups within the centre, strategies such as clearly communicate the procedures and interventions specific to each group and provide ongoing reminders throughout the study, maintain confidentiality regarding group assignments, and implement regular monitoring and supervision of the study activities will be adopted.

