### Intervention group

As shown in Figure 1, each subject in the intervention group will receive four Zoom video conference sessions and four telephone calls conducted by a nurse case manager (NCM) and a community worker (CW) who will be supervised by the NCM during the 3-month programme. In the first Zoom meeting, the NCM, who has more than 20 years of community elderly care experience, will comprehensively assess the health and social problems of the subjects using the Omaha System. The Omaha System is a holistic assessment tool that evaluates environmental, physiological, psychosocial, and health-related behaviours, and covers 42 problems [35]. For example, the problems of sanitation and residence belong to the environmental domain, while the problems of respiration and cognition belong to the physiological domain. After the problems are identified, the NCM will empower the subjects to set realistic goals; identify facilitators and barriers that may promote or hinder the achievement of these goals; provide health and self-care education; and build self-efficacy by verbal encouragement, recalling previous effective self-care strategies, and taking note of the beneficial effects of adopting self-care behaviour [28]. After the first Zoom meeting, the CW will follow-up with the subjects, under the supervision of the NCM, and evaluate their progress in achieving their goals. The CW will encourage the subjects to work on their self-care goals and maintain self-care behaviour and will provide information about the health and social activities that are organised by the community centre. To reduce the risk of infection during the coronavirus (COVID-19) pandemic, Zoom meetings and telephone calls will be used as the delivery channels.

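### Two eligible centre members from one household can be randomised separately, and the stated contamination measures do not reach the home

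*Protocol article*

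**What the plan says.** **Eligibility** (Study setting, subjects, and recruitment strategies). "Members of the community centre will be screened and recruited to the study if they (1) are aged at least 60 years", use a smartphone and reach the cognitive threshold. Six numbered exclusions follow. One removes people who do not live at home. Another removes those who "have already participated in another structured community health and social service partnership programme", which concerns a person's own past participation in a different programme. No criterion refers to a spouse, a co-resident or a household.

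**Allocation** (same section). "The subjects will be randomly assigned in a 1:1 ratio to either the intervention group or control group". Envelopes are opened in sequence, one for each call from the research assistant. No household unit or stratum is described.

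**Contamination** (same section). The article recognises contamination as a threat, and presents its strategies as directed at contamination inside the centre. They are clear communication of group-specific procedures, reminders, supervision, and a commitment to "maintain confidentiality regarding group assignments".

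**Delivery** (Intervention group). "each subject in the intervention group will receive four Zoom video conference sessions and four telephone calls". The content includes health and self-care education, goal setting and verbal encouragement.

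**The concern.** The safeguards are aimed at the centre, but the programme is delivered remotely. The article does not say where subjects take the sessions. The home is a reasonable inference, because people living in an area without Internet coverage are excluded. Education and encouragement given by video or telephone at home can be overheard and discussed by someone who lives there. Keeping assignments confidential is also hard to apply between two people who share a home.

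At stake is the between-group comparison of self-efficacy, quality of life and service use. A control who absorbs part of the programme moves the estimated difference towards zero. The Discussion section plans to extend the programme to six centres after this pilot, so an enrolment rule left unchanged here could carry over.

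**Working it through.** **Inputs from the article**
- Base size 30 per group, 20% drop-out, 36 per group, 72 in total (Sample size).
- Individual 1:1 allocation (Study setting, subjects, and recruitment strategies).

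**Inputs that are assumptions**
- Share f of subjects who enrol as co-resident pairs: 10%, 20% or 30%.
- Share c of the programme effect that passes to an exposed control: 0.5 or 1.
- Within-pair correlation (ICC): 0.1 to 0.5.

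**Step 1. The plan's own figure.** 30 × 1.20 = 36 per group, and 2 × 36 = 72, as stated. Dividing by the retained fraction gives 30/0.80 = 37.5, or 38 per group. That is a separate matter and does not affect this point: with 38 per group the split probability below would be 38/75 = 0.507, unchanged to three decimals.

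**Step 2. Chance that a pair is split.** With simple 1:1 randomisation it is 0.500. If exactly 36 are allocated to each arm, it is 36/71 = 0.507.

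**Step 3. Chance of at least one split pair** among k pairs under simple randomisation, 1 − 0.5^k: 75% for k = 2 and 94% for k = 4.

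**Step 4. Controls exposed.** Pairs = 72f/2. Split pairs = pairs × 36/71. Each split pair contributes one exposed control out of 36. Dilution = c × share of controls exposed.

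| f | Pairs | Split pairs | Controls exposed | Dilution, c = 1 | Dilution, c = 0.5 |
|---|---|---|---|---|---|
| 10% | 3.6 | 1.8 | 5% | 5% | 2.5% |
| 20% | 7.2 | 3.7 | 10% | 10% | 5% |
| 30% | 10.8 | 5.5 | 15% | 15% | 7.5% |

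**Step 5. Does pairing disturb the variance under the current allocation?** The variance factor for the difference in means is 1 + 2 × ICC × (same-arm pairs − split pairs)/72. A pair falls in the same arm with probability 35/71 and is split with probability 36/71, so the terms almost cancel. With 14 pairs and ICC 0.5: 1 + 2 × 0.5 × 14 × (35/71 − 36/71)/72 = 0.997.

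**Step 6. Variance cost of allocating pairs together.** All pairs are then in the same arm, so the factor is 1 + 2 × ICC × k/72. For k = 2 and ICC = 0.1 it is 1.006, about 1.01. For k = 14 and ICC = 0.5 it is 1.19.

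**The case against.** The strongest reply is that this is a condensed article, that a household rule may stand in the full protocol, and that the contamination strategies are introduced as examples. Nothing in the text is misstated or contradictory. That is fair, but the article does set out its eligibility criteria as a numbered list, its allocation method and the scope of its contamination measures. Followed as written, they allow split pairs and offer no stated protection at home.

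A second reply is that the effect is probably small. No document gives the number of pairs. The programme is individualised: the nurse assesses the subject's own problems, the goals are personal and referrals are made for that subject. A co-resident may overhear some education but receives none of the rest, so full transfer is an upper bound. With 30 completers per arm, the 95% confidence interval for a standardised difference has a half-width of about 2.00 × √(2/30) = 0.52. For an assumed effect of 0.3, a 10% dilution is 0.03. The sample size is a rule of thumb, so no power claim is undermined. All of this stands, and it limits the weight of the point.

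Three stronger readings are tempting and are not supported:
- A reader might infer that an older adult and a caregiver spouse would typically enrol together. The article says "The centre provides social activities to the community-dwelling older adults and support services to their informal caregivers", but not that caregivers are on the member list. Such a person would also have to meet every criterion. Two ordinary members who live together are enough for the point.
- A reader might infer that a split pair breaks the blind. The article blinds the research assistant and the centre staff. It claims no blinding of subjects.
- A reader might infer that correlated outcomes invalidate the planned t-test. Under individual allocation the effects of same-arm and split pairs nearly cancel (Step 5).

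**Conclusion.** The gap is real and its size is unknown. As written, the plan lets co-resident members enrol and be randomised separately, about half of such pairs would be split, and no stated measure addresses exposure at home. The bias is towards no difference. If 10% to 30% of subjects enrol as pairs, 5% to 15% of controls would be exposed. Those percentages are ceilings for the dilution and should not be read as its expected size; at half transfer they become 2.5% to 7.5%. Both the pair rates and the transfer share are assumptions. This is a design weakness that is cheap to remove. It is not a numerical error or an internal contradiction.

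**What to change.** **Preferred.** Add a question on co-residence to the screening call, record the answer, and allocate co-resident subjects together with one envelope. Account for the pair in the analysis, for example with a household random effect or household-clustered standard errors. Both baseline assessments should be complete before the envelope is opened, and the protocol needs a line for a co-resident who comes forward after the first has been allocated, because that person's arm would be known in advance. This removes split pairs and leaves eligibility and the recruitment-rate denominator for Reach unchanged. The cost is a design effect of about 1.01 to 1.19 under the assumed 2 to 14 pairs and ICC 0.1 to 0.5.

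**Alternative.** Enrol one member per household. This has no design effect but slightly reduces the pool. The recruitment rate is defined as subjects recruited divided by eligible subjects on the member list, so the rule must say whether the second co-resident is in that denominator. A person made ineligible by the rule cannot also be counted as eligible but not enrolled.

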### Outcome measures

RE-AIM [30] will be adopted as the evaluation framework of the programme. Of the five dimensions included in the RE-AIM framework, only effectiveness and maintenance outcomes will be collected from both the intervention and control groups. The outcomes of the other three dimensions—reach, adoption, and implementation—will only be collected from subjects in the intervention group.

To determine whether the programme reaches the target population, the recruitment rate and subject characteristics will be collected. The recruitment rate will be calculated by dividing the total number of subjects recruited by the total number of eligible subjects in the member list of the community centre.

Since this is a pilot study, we can only measure the effectiveness outcomes if such data can be collected. The Chinese version of the General Self-Efficacy Scale will be used to measure self-efficacy level. This scale has been validated in a Chinese population and has been shown to have good validity and reliability [36]. Version 2 of the 12-item Short Form Health Survey will be used to measure quality of life [37]. This scale measures various aspects of physical and mental health, from which physical and mental component scores will be calculated. It has been widely used, with good validity and reliability [37]. The total number of unscheduled general out-patient department, general practitioner, and emergency room visits and hospital admissions and the total number of attendances at health services will comprise the health service utilisation outcomes in this study. Health service utilisation information will be collected by the subjective reporting of the subjects and will be confirmed by examining the medical and attendance certificates. This data collection protocol has been shown to have good reliability [8].

We will explore the programme adoption by using semi-structured group interviews with the providers (i.e. the social workers and the NCMs), the involved centre staff members, and eight participants (i.e. 20% of the intervention group participants). In the interviews, the research assistant will explore the interviewee’s perceptions on the facilitating factors of and barriers to program adoption in the community centre. In addition, the research assistant will also audio-record and transcribe the conversation to examine the logistic and feasibility of the programme during the interdisciplinary care conferences.

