The extent to which the intervention is implemented as intended will be analysed using a performance checklist that records each step of the implementation process of the study. The checklist will be designed and completed by the PI, who will not be involved in implementing the intervention.

The maintenance effects of the intervention will be measured by repeating the measurement of effectiveness outcomes at three months following the completion of the intervention if such data can be collected.

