### Data collection

Quantitative data will be collected at baseline, before the commencement of the programme (T1); immediately post-intervention (T2); and 3 months after the completion of the intervention, to evaluate the maintenance of the programme (T3). A trained RA who is blinded to the group assignment will call the subjects to collect these data.

Three separate semi-structured interviews will be conducted at T2 to collect qualitative data from all centre staff and service providers (i.e. nurse case managers and social workers) and 20% of the intervention group subjects (i.e. 8 subjects).

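### The Hong Kong residence criterion covers 3 months, but the maintenance outcomes are due at about 6 months, so members who know they will be away then are still eligible

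*Protocol article*

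**What the plan says.** **Eligibility** (Study setting, subjects, and recruitment strategies): the last of six exclusions applies to people who "will not be staying in Hong Kong for the next 3 months". The starting point of that window is not given.

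**Programme length** (Intervention group): contacts are delivered by the nurse case manager and a community worker "who will be supervised by the NCM during the 3-month programme".

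**Maintenance outcome**: the Objectives define it as "sustained programme effects at 6 months". Outcome measures says the effectiveness outcomes are repeated "at three months following the completion of the intervention if such data can be collected". Data collection gives the same timing for T3.

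**How the data are obtained**: a blinded research assistant "will call the subjects to collect these data" (Data collection). Health service use is self-reported and then "confirmed by examining the medical and attendance certificates" (Outcome measures).

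**The concern.** An availability criterion is normally set so that people admitted to the trial can be assessed at every planned time point, as far as can be foreseen. Here it spans only the length of the intervention. A member who says at screening that they will leave Hong Kong in month 4 meets every listed criterion, although one of the five RE-AIM dimensions is assessed on them at about month 6.

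Maintenance is also one of only two dimensions measured in both arms. At stake are its completeness and, for health service utilisation, its comparability between subjects who were in Hong Kong throughout the period and subjects who were not.

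**Working it through.** **1. The time windows.**
- Residence required by exclusion (6): 3 months.
- T2, immediately after the programme: month 3.
- T3: 3 + 3 = 6 months from programme start, which agrees with the 6 months in the Objectives.
- Uncovered time: 6 − 3 = 3 months, which is the whole maintenance period if the residence window starts with the programme.

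**2. Does another criterion close the gap?** The inclusion criteria concern age, smartphone use and the HK-MoCA score. The other exclusions concern ability to communicate, not living at home, being bedbound, Internet coverage and earlier participation in a similar programme. None concerns presence or availability between months 3 and 6.

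**3. Which outcomes need presence in Hong Kong?**
- Self-efficacy and SF-12: questionnaire scores taken by telephone. Being away does not by itself make them missing.
- Health service utilisation: a count accumulated over time and checked against certificates. As an illustration, assume that the T3 count covers the 3 months since T2, that only visits in Hong Kong are counted, and that the visit rate is constant. A subject who leaves at month 4 and does not return is then present for 1 of 3 months, so the expected count is 1/3 of what full presence would give. If visits elsewhere are counted too, the shortfall may be smaller, but the services differ and the certificates are harder to examine. The article does not say which visits count.

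**4. How many subjects?** The plan's own sample size is reproduced by 30 × 1.20 = 36 per group, 72 in total. That leaves 36 − 30 = 6 losses per group before the stated minimum of 30 is reached. The document gives no share of members who will be away in months 3 to 6. Purely as an assumption, 0% to 10% of 36 gives 0 to 3.6 subjects per group. This is an upper bound on what the criterion could prevent, for two reasons: only those who know of their absence at screening could be screened out, and some of those away would still give usable T3 data by telephone.

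**5. Direction between arms.** Eligibility is settled before 1:1 randomisation, so planned absences are expected equally in both groups, apart from chance.

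**The case against.** The strongest reply is that the window was matched to the intervention on purpose. The programme relies on local referrals and centre activities for 3 months, and follow-up needs only a telephone. This stands for self-efficacy and SF-12, and it limits the point largely to utilisation. Even there, the article defines utilisation as self-reported totals and does not restrict them to Hong Kong, so the distortion is plausible but not documented.

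The plan also tempers its expectations. It is a pilot sized by a rule of thumb, it collects maintenance data only where possible, and it allows 20% drop-out against about 15% in an earlier study. Some departures may already fall within that allowance. This stands as a limit on size. It is not a reason to enrol people whose absence at T3 is already known.

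A reader might infer three stronger things that the document does not support:
- **That T3 will be missing for everyone who leaves.** Telephone collection contradicts this.
- **That the comparison between arms is biased.** The criterion acts before randomisation, and nothing in the text points to differential absence.
- **That the window fails to reach even T2.** This would follow if the 3 months ran from screening, because the telephone call, home visit, consent, baseline and randomisation come before the programme. Neither the start of the window nor the length of that lead-in is stated, so it remains only a possibility.

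**Conclusion.** The mismatch is certain from the text: 3 months of required residence against a last assessment at about 6 months, with no other criterion covering the difference. Its consequence is small. It allows some avoidable missing data and lost precision at T3, mainly in health service utilisation, where counts may also not be comparable. That utilisation is the most exposed outcome rests on two assumptions: that time away changes the visits counted, and that it makes certificates harder to examine. The number of subjects affected cannot be derived from the document, and the 0 to 3.6 per group above is only an illustration. The sample size calculation is not in question on this point. The change is worth making because it is cheap and maintenance is a stated objective, not because the pilot's conclusions depend on it.

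**What to change.** Reword exclusion (6) so that it covers the period up to the T3 assessment, about 6 months from programme start, and state that the period is counted from baseline or randomisation. Record days away from Hong Kong in each utilisation period, so that counts can be read against time present, including for subjects whose absence was not foreseen.

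Cost: a short change to one criterion, by amendment if recruitment has begun, and one extra data item at the follow-up calls. A few otherwise eligible members would be excluded. Because the recruitment rate divides recruits by eligible members on the centre's list, its denominator would change slightly. The sample size stays as it is.
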